## Abstract

**Background:**

Data on the routine use of video-assisted laryngoscopy in peri-operative intubations are rather inconsistent and ambiguous, in part due to small populations and non-uniform outcome measures in past trials. Failed or prolonged intubation procedures are a reason for relevant morbidity and mortality. This study aims to determine whether video-assisted laryngoscopy (with both Macintosh-shaped and hyperangulated blades) is at least equal to the standard method of direct laryngoscopy with respect to the first-pass success rate. Furthermore, validated tools from the field of human factors will be applied to examine within-team communication and task load during this critical medical procedure.

**Methods:**

In this randomized, controlled, three-armed parallel group design, multi-centre trial, a total of more than 2500 adult patients scheduled for perioperative endotracheal intubation will be randomized. In equally large arms, video-assisted laryngoscopy with a Macintosh-shaped or a hyperangulated blade will be compared to the standard of care (direct laryngoscopy with Macintosh blade). In a pre-defined hierarchical analysis, we will test the primary outcome for non-inferiority first. If this goal should be met, the design and projected statistical power also allow for subsequent testing for superiority of one of the interventions.

Various secondary outcomes will account for patient safety considerations as well as human factors interactions within the provider team and will allow for further exploratory data analysis and hypothesis generation.

**Discussion:**

This randomized controlled trial will provide a solid base of data in a field where reliable evidence is of major clinical importance. With thousands of endotracheal intubations performed every day in operating rooms around the world, every bit of performance improvement translates into increased patient safety and comfort and may eventually prevent significant burden of disease. Therefore, we feel confident that a large trial has the potential to considerably benefit patients and anaesthetists alike.

**Trial registration:**

ClincalTrials.gov NCT05228288.

**Protocol version:**

1.1, November 15, 2021.

## Background

### Rationale

Endotracheal intubation is the gold standard for airway management under general anaesthesia. Over the course of the past several years, video-assisted laryngoscopy (VAL) has more and more gained in importance in this field and has already found its way into the relevant guidelines for certain settings and situations like the unexpected difficult airway [1], critically ill patients [2] or prehospital airway management [3]. Although VAL is attested superiority especially in unexpected difficult airways, known difficult airways, and obese patients in some studies [4–6], inconsistent results in the different studies and sometimes very small patient populations make clear recommendations difficult apropos further generalisability [5].

While video laryngoscopes already significantly expand the field of view simply by positioning the camera, hyper-angulated blades can also accommodate significantly greater curvatures of the pharyngeal anatomy of certain patients where a direct view of the glottis plane would otherwise not be possible [7]. This has further increased success rates in selected patient collectives.

VAL has tended to be superior to direct laryngoscopy in terms of safety in the studies conducted to date, but the quality of evidence based on the existing studies is still insufficient to draw definitive conclusions [5]. Thus, despite the enormous clinical relevance of the question [8, 9], insufficient solid data currently exist to make conclusive recommendations for or against the standard use of VAL in daily anaesthesiologic practice. One reason for the insufficient evidence certainly is the frequently inconsistent or inappropriate selection of endpoints in previous studies [10–13].

A Cochrane systematic review with a total of 64 included studies concluded that primary endotracheal intubation using a video laryngoscope leads to a lower number of failed attempts in emergency scenarios, especially in patients with an expectedly difficult airway [5]. However, the evidence listed for this finding according to the Grading of Recommendations, Assessment, Development and Evaluations (GRADE) system is reported to be only moderate. Furthermore, it is indicated that VAL can be used to improve the view of the glottis and vocal fold plane. VAL could achieve significantly lower Cormack & Lehane scores [14] and reduce the number of grades 3 and 4, equivalent to significantly poorer glottic visibility. A significant improvement of the Cormack & Lehane grade using VAL was also confirmed in a multi-centre study by Kaplan et al. [15]. In addition, VAL has been attributed with potential advantages in terms of handling and a lower incidence of mucosal, laryngeal, and tracheal damage, as well as a lower incidence of hoarseness compared to conventional laryngoscopy [16]. In contrast, no statistically significant differences are described between the different devices with respect to either the first-attempt success rate or the total number of intubation attempts required. The same applies to the occurrence of hypoxia and other respiratory complications. The authors point out that the evidence for these findings must be considered very low due to a lack of robust data. Moreover, many endpoints, such as time to successful intubation, are difficult to evaluate in a meta-analysis due to heterogeneous definitions and lack of comparability.

VAL has been included in the guidelines for airway management of the respective professional societies with different recommendations. For the perioperative setting, VAL is mentioned as a back-up procedure in the German guidelines, e.g. in case of an unexpectedly difficult airway after max. two conventional laryngoscopy attempts as well as in obese patients [13]. In the field of obstetric anaesthesia, the recent S1 guideline calls for VAL to be available and also considers its use as a primary device to be an option: “A video laryngoscope can facilitate airway management in pregnant women in the context of an RSI and may also be considered as a first-choice method” [17]. In contrast, the current guideline on prehospital emergency anaesthesia with endotracheal intubation recommends the use of a video laryngoscope as the primary tool [3]. In current meta-analyses, primary success rates for endotracheal intubation are regularly reported to be slightly higher for VAL (> 90%) than for conventional laryngoscopy (< 90%) [4, 6, 16, 18].

Going beyond the mere procedure of endotracheal intubation, i.e. inserting a tube in the trachea, this study also aims to descriptively investigate the domain of human factors in the context of critical medical interventions using the example of airway management. In general, this aspect, which examines psychological and physiological influences (among others) on process functioning, is still largely left out of anaesthesiologic research. However, a 2013 study concluded that in all cases in which anaesthesiologists had reported serious airway rescue incidents to a relevant registry, such human factors had contributed to the errors that occurred [19]. In the context of intensive care medicine [20, 21] or simulation training [22], individual reports have been published so far, but data from large collectives are still lacking. For this reason, in this study, after each intervention, the performing anaesthesiologist and the collaborating nurse will be asked to complete two brief, validated questionnaires to capture human factors-relevant observations and assessments: The Mayo High Performance Teamwork Scale (MHPTS) [23] and the NASA Task Load Index (NASA-TLX) [24].

The MHPTS consists of 16 individual items that describe a representative number of characteristic nontechnical crew resource management (CRM) behaviours for high-performance teamwork and can be rated using a 3-point scale (0 = never/almost never, 1 = alternating/inconsistent, 2 = constant/consistent). It thus provides a brief, validated, and practical rating scale that can be used by CRM-inexperienced team members in a high-performance medical setting to reflect on important CRM skills and evaluate their own team performance. The NASA-TLX assesses subjectively perceived stress while completing a task on a visual analogue scale (VAS) in six domains [24]. The NASA-TLX is widely used in the field of human factors research and has been used in scientific studies in the field of surgery, for example [25].

### Hypothesis and experimental approach

Based on the data available to date, it can be assumed that VAL is at least equivalent to direct laryngoscopy also in the context of elective intubations but could increase patient safety in special situations. Therefore, this trial implements a three-arm, parallel group, randomized-controlled design to investigate the hypothesis that VAL is primarily non-inferior to conventional laryngoscopy in terms of the rate of successful intubations at first attempt. In this study, patients are randomized to one of three parallel study arms: in the first arm, the patient is primarily intubated using conventional, direct laryngoscopy with a Macintosh blade. This intervention, thus far considered the gold standard, also represents the control group. In a second arm, patients will be intubated by VAL, also using a Macintosh-shaped blade. In the third study arm, the primary instrument to be used will be a video-assisted laryngoscope, where primarily and regardless of possibly known difficult airway, a hyper-angulated blade will be used.

We hypothesize that the procedure “video-assisted laryngoscopy”, i.e. both VAL study arms taken together in a first analysis step, is non-inferior to the “conventional laryngoscopy” control group regarding the primary endpoint “successful intubation at first attempt”. If this first attempt fails, the decision on the laryngoscopy procedure to be used in the further course is the sole responsibility of the anaesthesiologist performing the procedure; for reasons of patient safety, the study protocol does not contain any provisions in this regard, and the procedure primarily used according to randomization can be abandoned without consequence for study participation.

### Benefit-risk assessment

All patients receive the medically necessary peri-operative care. According to current knowledge, randomization into one of the three study arms does not per se entail any altered risk for participants. Both conventional laryngoscopy and VAL are established as standard clinical procedures. The fact that, according to the current state of knowledge, no procedure is superior to the other for elective endotracheal intubation in the context of general anaesthesia is precisely the subject of this study. There is no evidence from the data available in the literature to suggest that VAL may expose the patient to additional risk compared with the conventional procedure.

Since both investigated laryngoscopy procedures are used in routine clinical practice, but sufficient robust data to demonstrate the superiority of either procedure have been lacking to date, the investigation of this issue in a randomized-controlled clinical trial with the aim of maximizing patient safety during a potentially life-threatening intervention also appears to be ethically appropriate. No increased risk results for the patient from participation in this clinical study, neither is a direct medical benefit for the patient assumed resulting from participating.

### Choice of comparators

In this study, three different modalities of laryngoscopy for endotracheal intubation will be compared (s. Fig. 1): 1. conventional, direct laryngoscopy using a Macintosh blade. This procedure is considered the gold standard and is routinely used in the peri-operative setting as well as in intensive care and emergency medicine. 2. use of VAL with a Macintosh-shaped blade. By positioning the camera at the tip of the blade, the field of view onto the glottic plane is improved, as there is no need to establish a direct line of sight from the outside to the tracheal inlet (as is the case with conventional laryngoscopy). 3. use of VAL with a hyper-angulated blade. This shape of laryngoscope blade cannot be used in conventional, direct laryngoscopy because the strong curvature renders a direct line of view from the outside impossible due to the geometry of the instrument. So far, hyper-angulated blades are often used as a backup instrument when a view of the glottic plane cannot be achieved with the Macintosh blade due to anatomic abnormalities, even with a video-assisted laryngoscope. This often enables endotracheal intubation in patients who could otherwise not be intubated through conventional laryngoscopy. At the same time, however, it is conceivable that the rather extreme curvature of the blade may prove disadvantageous in individual cases compared with less curved blade variants. This may be because insertion of the tube is difficult due to the curvature of the blade and indirect vision, or because fluids like mucus or blood make it impossible to see through the video-optical system.

**Fig. 1 Fig1:**
[figure not shown]
Examples of different laryngoscopes to be used in each of the three study arms (from left to right): conventional laryngoscope with Macintosh blade, video-assisted laryngoscope with Macintosh-shaped blade, video-assisted laryngoscope with hyper-angulated blade

After testing the non-inferiority of the experimental intervention (VAL as an overall procedure) compared with the control group, pairwise comparisons between the study arms will also be of interest. If this step of the hierarchical analysis plan can be reached, testing for superiority between groups will be possible. Furthermore, the question of whether the primary use of a hyper-angulated blade may be useful can be explored. In this scenario, for example, the hyper-angulated blade would not be inferior in the general setting, but would possibly make a second intubation attempt, or a change of the device used, unnecessary in the case of an unexpectedly difficult airway, since the “rescue device” has already been used to begin with.

### Aims of the study

#### Primary aim

The primary aim of this trial is to study whether VAL is non-inferior to conventional laryngoscopy for endotracheal intubation in the context of elective surgery under general anaesthesia. Non-inferiority hereby refers to the average rate of successful intubations at first attempt from all interventions in a study arm.

#### Further aims

In addition, several other parameters will be collected, which, individually or in combination, can provide insights into the risk–benefit profile of the interventions examined. In case of previously proven non-inferiority as laid out in the primary hypothesis, substantial differences between the procedures regarding accompanying injuries, critical changes in vital parameters during intubation, etc., may hint towards a general advantage of one procedure over the others.

Furthermore, perceived task load and the quality of the information flow within the team of care providers (mostly anaesthetists and specialist nurses) shall be assessed using structured, validated questionnaires. The underlying hypothesis is that VAL, through the progress of the intubation process being visible to all involved, simplifies supportive or anticipatory measures by the specialist nursing staff and improves the non-verbal information flow.

Ultimately, the primary intention of this study is to determine whether there is a generally recommended instrument that is non-inferior in the uncomplicated airway but possibly causes fewer complications in the (unexpected) difficult airway.

## Methods and design

### Design

This is a randomized controlled multi-centre study with a three-arm parallel study design (s. Fig. 2). The primary endpoint is the successful placement of the endo- tracheal tube at first attempt (success at first attempt) as a dichotomous feature. The patients included in the study will be evenly distributed across the three study arms (1:1:1). The underlying approach is the premise of non-inferiority of the experimental interventions compared to the established standard procedure.

**Fig. 2 Fig2:**
[figure not shown]
Flow diagram

The “conventional laryngoscopy” study arm serves as a control group in this experimental setup. The two study arms using VAL will initially be combined at the first stage of the analysis to show that the method “VAL” is non-inferior to the established gold standard regardless of the blades used. If this first analysis can prove non-inferiority, the three individual groups will also be compared against each other.

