### Statistical analysis

The primary outcome is the rate of successful intubations at first attempt as a fraction of dichotomous events. In a first analysis step we test the hypothesis, that neither video assisted laryngoscopy with a Macintosh-shaped blade (M-VAL) nor video assisted laryngoscopy with a hyper-angulated blade (H-VAL) are inferior to conventional direct laryngoscopy (CDL) with regard to the primary outcome. In terms of the statistics, this corresponds to testing the Null hypothesis that at least one of the interventions M-VAL or H-VAL is inferior to CDL. Both Null hypotheses will be tested for separately. The overall type-I error will be set to 5%. Thus, both Null hypotheses will be tested on a local significance level of 0.025 using a one-sided Z-test with unpooled variance. Non-inferiority is defined as described in subsection “sample size”.

Only if both Null hypotheses can be rejected will there be a second analysis step where the single interventions M-VAL and H-VAL will be tested pairwise for superiority using a two-sided Z-test with unpooled variance. As we apply the principle of fixed sequence hierarchical testing, this analysis can be performed at a local significance level of 0.05 to meet the family-wise error rate of 0.05.

A planned interim analysis will be conducted after 200 randomized interventions. This will first and foremost happen to review feasibility and data quality before expanding to additional study sites. We do not foresee any substantial safety concerns in this trial which would need to be assessed at this stage.

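### The first confirmatory step is defined both as pooled VAL versus direct laryngoscopy and as two separate blade-level tests, and the pooled form can pass when one blade is inferior

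*Protocol article*

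**What the plan says.** Three sections of the protocol article describe a pooled first step:

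- Hypothesis and experimental approach: the hypothesis concerns VAL with "both VAL study arms taken together in a first analysis step".
- Choice of comparators (text after Fig. 1): pairwise comparisons come "After testing the non-inferiority of the experimental intervention (VAL as an overall procedure) compared with the control group".
- Design (text after Fig. 2): "The two study arms using VAL will initially be combined at the first stage of the analysis", with the aim of showing that VAL "is non-inferior to the established gold standard regardless of the blades used". The three groups are compared with each other only if this succeeds.

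Two sections describe separate tests:

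- Statistical analysis: the first step is "testing the Null hypothesis that at least one of the interventions M-VAL or H-VAL is inferior to CDL". It adds "Both Null hypotheses will be tested for separately", each by a one-sided Z-test with unpooled variance at 0.025. The gate is strict: "Only if both Null hypotheses can be rejected will there be a second analysis step".
- Sample size: the calculation rests on two null hypotheses tested separately at 2.5% each, with 90% success in all groups, a 5% difference and 90% power.

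No section reconciles the two descriptions or says which prevails.

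**The concern.** The two rules differ in null hypothesis, in power and in the gate to the superiority step. The pooled rule asks whether the average of the two VAL success rates is within 5 points of CDL. The separate rule asks whether each rate is. A good result with the Macintosh-shaped blade can offset a poor result with the hyper-angulated one under the first rule but not under the second. The Choice of comparators section itself allows that the strong curvature may be a disadvantage in individual cases.

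Two things are at stake. First, the same data can give opposite headline conclusions, and the document leaves room to choose between them once results are known. Second, if the pooled test is used to support a statement that holds whichever blade is used, the type-I error of that statement is not controlled.

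**Working it through.** **Inputs.** From Sample size and Statistical analysis: success rate 90%, margin 0.05, one-sided local level 0.025 (z = 1.960), power 90% (z = 1.282), unpooled variance. From Design: 1:1:1 allocation.

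**The plan's own sample size.** For one VAL arm against CDL:

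n = (1.960 + 1.282)² × (0.9×0.1 + 0.9×0.1) / 0.05² = 756.5, so 757 per arm and 2271 in total.

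The protocol prints 3 × 824 = 2526, but 3 × 824 = 2472, while 2526/3 = 842. The total is recovered if an unstated 10% loss is assumed: 757/0.9 = 841.1, rounded up to 842, and 3 × 842 = 2526. A pooled 2:1 comparison would need only (1.960 + 1.282)² × (0.09 + 0.09/2) / 0.05² = 567.4, so 568 per arm. The stated total therefore fits the separate-test design. I use n = 842 below; with 824 the results change by about one percentage point at most.

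**Formulas.** With true rates c (CDL), m (M-VAL), h (H-VAL):

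- Pooled test: difference D = (m + h)/2 − c; SE² = c(1−c)/n + [m(1−m) + h(1−h)]/(4n).
- H-VAL test: D = h − c; SE² = c(1−c)/n + h(1−h)/n.
- In each case P(pass) = Φ[(D + 0.05)/SE − 1.960].
- Both separate tests: bivariate normal probability, with the correlation induced by the shared control arm.

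**Worked example**, c = 0.90, m = 0.93, h = 0.85:

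- Pooled: D = 0.89 − 0.90 = −0.01; SE = 0.0128; (0.04/0.0128) − 1.960 ≈ 1.16; P = 88%.
- H-VAL: D = −0.05; the numerator is 0; P = Φ(−1.960) = 2.5%.

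**Results**, CDL 90%, n = 842 per arm. The protocol assumes 90% in all groups; every other VAL rate is my assumption.

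| M-VAL | H-VAL | Pooled test passes | Both separate tests pass |
|---|---|---|---|
| 90% | 90% | 97.7% | 87.6% |
| 90% | 85% (at margin) | 48% | 2.5% |
| 93% | 85% (at margin) | 88% | 2.5% |
| 95% | 85% (at margin) | 98% | 2.5% |
| 94% | 84% (beyond margin) | 88% | 0.5% |

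Simulation of 400,000 trials agreed where it was run: for 90%/85% it gave 47.8% pooled and 2.6% for both tests, and for 95%/85% it gave 98.3% and 2.5%.

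**Opposite verdicts from one data set.** Suppose the observed rates are CDL 90%, M-VAL 92%, H-VAL 87%.

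- Pooled: −0.5 points, SE 1.27, lower bound −0.5 − 1.96×1.27 = −3.0 points, above −5: pass.
- H-VAL: −3.0 points, SE 1.55, lower bound −3.0 − 1.96×1.55 = −6.0 points, below −5: fail.

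The pooled rule declares success and opens the next step. The separate rule does neither.

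**The case against.** The strongest reply is that only one of the two analyses is operational. The separate tests have a null hypothesis, test statistic, local level, gate and sample size. The pooled test has no significance level, no statistic and no sample size; it appears only in narrative sections, and the 0.025 applied to it above is my choice. At 0.05 its pass rate for 90%/85% would be 60% instead of 48%. All of this is right. It shows which version the sponsor should keep, but it does not remove the conflict. The pooled version is the one stated in the formal hypothesis, and the Further aims section makes the reading of the secondary outcomes depend on non-inferiority under that hypothesis.

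Second, the wording about blades under Design may mean only that blades are not distinguished, in which case a pooled test is valid for that average claim. The reading is possible. It would still be a different claim from the one in Statistical analysis.

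Third, the groups are compared individually afterwards, so a poor H-VAL result would usually be seen. With M-VAL 93% and H-VAL 85%, a two-sided 0.05 test of H-VAL against CDL has about 87.5% power. This softens the practical harm, but the primary verdict would already have been declared.

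Fourth, analysts are blinded to allocation. That limits bias but does not fix which hypothesis is primary.

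**Conclusion.** The point holds. The protocol states two incompatible primary analyses and does not rank them. With one blade exactly at the 5-point margin, the pooled rule passes in 48% to 98% of trials as M-VAL goes from 90% to 95%; the separate rule passes in 2.5%. Even under the protocol's own assumption of 90% everywhere, the pass rates are 97.7% and 87.6%, so the verdicts differ in at least 10% of trials (97.7 − 87.6 = 10.1 points).

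These figures rest on 842 per arm, the normal approximation, one-sided 0.025 for the pooled test and assumed VAL rates. The error inflation is conditional on following the pooled wording; under the Statistical analysis section the chance of passing with one inferior blade stays at about 2.5% or less. It must be fixed because the choice between the rules decides the main conclusion.

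**What to change.** Make the procedure in Statistical analysis the only primary analysis: M-VAL versus CDL and H-VAL versus CDL tested separately for non-inferiority, with both required before claiming that VAL is non-inferior irrespective of blade. Amend Hypothesis and experimental approach, Choice of comparators and Design to say the same. Any pooled VAL versus CDL estimate should be labelled descriptive and reported after the two separate results.

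The cost is a wording amendment before unblinding, with no new patients or data. The pooled test's power of about 98% is given up, but it answers a different question. The amendment should also say that the planned 90% power applies to each comparison: the power to pass both tests is 87.6% at 842 per arm and 83.3% at 757. That shortfall already follows from the current gate and is not created by this change.
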